### Study Design

This is a multi-stage and prospective study. It includes the following three stages:

The first stage is a cross-sectional study, based on the baseline information from 6,800 community-dwelling elderly adults collected through a set of questionnaires. The aim of the first stage is to investigate the epidemiological characteristics of LLD in northern China, and to explore the biological, psychological, and social risk factors for developing LLD.The second stage involves statistical analysis, with the aim of constructing a risk factor model for LLD and analyzing direct and indirect functional routes on the basis of structural equation modeling (SEM).The third stage is an experimental study, comprising a 6-month supportive intervention period and a 6-month follow-up period. In order to ensure the participation of the subjects in this study and improve the effectiveness of the interventions, a total of 60 elderly patients with depression and their principle caregivers will be randomly and equally assigned to trial and control groups.

Trial group patients and caregivers will undergo supportive PDH interventions, and control group patients and caregivers will receive TAR. Subsequently, depressive symptoms, QOL, and the social and cognitive functioning of the patients in the two groups will be respectively assessed at a baseline and after 6, 9, and 12 months post-intervention by using scales and questionnaires to analyze the effectiveness of the supportive PDH intervention measures. Ultimately, an SIHM model will be constructed by combining PDH intervention with mental health institutions, CHS, and aging families as the main line.

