Form	P: Supportive psychosocial intervention Rely on the platform of CHS to carry out group psychological intervention for patients. Rely on the family, and have intervention team members work with the principle caregivers to provide psychological counseling and personalized treatment for patients. H: Supportive health education Distribute manuals and pamphlets on the prevention and treatment of depression in the elderly. Regularly carry out group discussions and lectures for patients and their principle caregivers. Open a psychological consultation platform on the Internet. Cooperate with CHS to establish an LLD rehabilitation self-help group and organize group activities regularly. (group therapy will be conducted once a month, and family and individual therapy will be conducted at least twice a month)
Method	Make physical examination appointments or temporary on-site appointments with patients and their principle caregivers. Collect patient health information and establish health management files. Health assessment and prediction, with a detailed intervention plan. Pre-intervention training. The project leader and main group members will conduct unified training for follow-up CHS members. The main content of the training will pertain to symptoms and condition assessments, medication and efficacy observations, physical and mental health recording, interviewing skills, psychosocial intervention methods, and home visits and telephone follow-up skills. Intervention. The follow-up members should strictly follow the intervention outline formulated by the research group and adopt the supportive PDH method to complete the intervention. The project team will arrange fixed personnel to supervise and guide the members regularly. Overall, the intervention will last 6 months. Follow-up. In the first 3 months after the intervention, a monthly home visit and a telephone follow-up will be conducted. A telephone follow-up will be conducted every 2 weeks for the next 3 months, where the follow-up period will last 6 months. During each follow-up, it is necessary to evaluate the health management status of the patients and any intervention goals that have been achieved, while devising new goals based on the actual situation, and providing corresponding individual counseling according to the patients' mastery of relevant knowledge, skills, and personal needs.

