### Sample Size, Power, and Effect Size

The primary goals of this study are to analyze the epidemiological characteristics and construct a risk model for LLD in Liaoning. The study design for this part is a cross-sectional study. Wang et al. reported the prevalence of MDD in elderly Chinese at 2.8%, where the ratio of urban to rural was 1.4:1 (10). That is, if the testing level α and the relative error ϵ are set to 0.05 and 0.15P, 6179 community-residing elderly adults are expected to enroll, according to the following equation (32):

$$\text{N}=[Z_{a/2}^{2}P(1-P)]/\epsilon^{2}$$

Given that 10% of the data are missing, a total of 6,800 elderly residents (approximately 3414 urban residents and 3,386 rural residents) should be included.

The secondary goals of this study are to conduct and evaluate integrated supportive PDH interventions and TAR for the objects in the trial group and control group, respectively. The study design for this part is an experimental study, and the sample size can be determined by the change in the value of the mean and standard deviation of the depression score of elderly patients before and after intervention in a previous study (33). That is, if the testing level α and type-II error β are set as 0.05 and 0.10, respectively, the sample size of the trial group and control group will be roughly 25 in both cases, according to the following equation (32):

$${\text{N}}_{1}={\text{N}}_{2}=2[\frac{({\text{z}}_{\alpha /2}+{\text{z}}_{\beta })\sigma }{\sigma }{]}^{2}$$

Given that 20% of the data are missing, each group should have a sample size of 30 LLD patients. Meanwhile, to facilitate the compliance of patients in the later intervention stages, and to ensure the effectiveness of the intervention, each patient’s primary caregiver will be required to accompany the participant. In the later stages, we will further revise the sample size according to the preliminary experimental results from the intervention study.

The participants, method, assessment time, and data collection administrators are listed in **Table 3**.

**Table 3 T3:** Data collection at baseline and follow-up evaluation.

Domain	Measure	Participants	Method	Assessment time	Administrator
Informed consent	Informed consent	All participants ^b^	Interview	Screening	Investigator
Eligibility	Inclusion/Exclusion	All participants ^b^	Interview	Screening	Investigator
Psychiatric diagnoses	MINI	All participants ^b^	Interview	Screening	Investigator

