### Data Preprocessing and Statistical Analysis

The statistical analyses will be performed by employing the SPSS statistical package, version 20.0 (SPSS Inc., Chicago, IL, USA), and all evaluations of significance will be determined based on two-sided tests using the 0.05 level of statistical significance. In addition, missing values will be replaced by the column mean/median in this study. The details of the analytic approach are as follows.

Demographic and clinical characteristics, lifestyle patterns, medical history, history of alcohol and drug abuse or dependence, family history of mental illness, self-knowledge and treatment attitude, and the self-efficacy levels and depressive symptoms of the subjects will be described by frequency distribution, percentage, arithmetic mean, and standard deviation.Comparison of the above variables between patients with or without LLD will be made using the independent-sample *t*-test, Mann–Whitney *U*-test, and the chi-squared test, as appropriate.Correlation analysis, logistic regression (for binary variables), and multiple linear regression (ANCOVA for continuous variables) will be used to determine whether the variables can enter SEM, and to test the direct and indirect pathways among these hypothesized determinants.Amos version 22.0 statistical software will be used for SEM of the risk factors for LLD.GDS, SDSS, SF-36, OPQOL, Family APGAR, GSES, IBS, MoCA, and the related KAP for LLD in the elderly will be used as evaluation indices, and analysis of variance (ANOVA) will be applied to compare the results of the control and the trial groups before and after intervention.Regression analysis will be used to analyze the influence of various factors on the effectiveness of the supportive PDH intervention.

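### PDH is delivered partly in therapy groups and no such groups are described for TAR, yet the sample size and the ANOVA treat all patients as independent; if outcomes correlate within groups, the standard error is too small and the 90% power is overstated

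*Protocol article*

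**What the plan says.** - **Delivery in the PDH arm.** Table 2 lists group nostalgia therapy among the contents. Its Form row adds group psychological intervention on the community health service platform, group discussions and lectures, and a self-help group. On frequency it says that "group therapy will be conducted once a month, and family and individual therapy will be conducted at least twice a month". The intervention lasts 6 months.
- **Control arm.** The Abstract defines TAR as drug treatment and health education. No therapy groups are described for it, and the form of its health education is not stated.
- **Allocation.** Under Study Design, 60 patients with their caregivers "will be randomly and equally assigned to trial and control groups".
- **Sample size.** Under Sample Size, Power, and Effect Size, the formula is the usual one for two independent means. Its inputs are "determined by the change in the value of the mean and standard deviation of the depression score of elderly patients before and after intervention", taken from a cited study, without figures. The text continues "if the testing level α and type-II error β are set as 0.05 and 0.10, respectively", and concludes that "the sample size of the trial group and control group will be roughly 25 in both cases". Then: "Given that 20% of the data are missing, each group should have a sample size of 30 LLD patients". There is no design effect.
- **Analysis.** Under Data Preprocessing and Statistical Analysis, "analysis of variance (ANOVA) will be applied to compare the results of the control and the trial groups before and after intervention", and "all evaluations of significance will be determined based on two-sided tests using the 0.05 level of statistical significance". No term for therapy group is named.

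The number of groups, their size, their leaders and any ICC appear nowhere in the article.

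**The concern.** Patients treated in the same group share sessions and each other's company, and probably a leader, so their outcomes may be more alike than those of patients in different groups. This trial is individually randomised but partially nested: the possible clustering arises in one arm only. The variance of the PDH mean then contains a between-group component that a formula for independent patients leaves out.

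Two things are at stake for the GDS comparison. The ANOVA would reject a true null hypothesis more often than the nominal 5%. A test that keeps its level would have less than the planned 90% power. With only 60 patients there is little room to absorb either.

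**Working it through.** **Inputs from the article:** two-sided alpha 0.05, beta 0.10, about 25 per arm analysed, 30 per arm enrolled.

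**Assumed, because the article gives no figure:** ICC 0.01 to 0.10 and group size m = 8 to 15. The range for m has some support. The sampling for this phase takes one district and one township in Shenyang, then one urban and one village community from each, which can be read as two to four communities. If groups follow communities, 30 PDH patients give 30/4 = 7.5 to 30/2 = 15 per group.

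**Step 1: the plan's own figure.** The effect size is not printed, so 25 cannot be rebuilt forwards. Solving backwards from n = 2[(z_alpha/2 + z_beta) × SD/delta]² with n = 25:

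delta/SD = sqrt(2 × (1.960 + 1.282)²/25) = 0.917.

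With independent outcomes this gives power Phi(0.917 × sqrt(12.5) − 1.96) = Phi(3.24 − 1.96) = 90%. The allowance for missing data is 25 × 1.2 = 30.

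**Step 2: clustering in the PDH arm only, total SD held constant.**

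- Design effect in PDH: DE = 1 + (m − 1) × ICC
- True SE divided by ANOVA SE: r = sqrt((1 + DE)/2)
- Type I error of the ANOVA: 2 × [1 − Phi(1.96/r)]
- Power with the correct SE: Phi(3.24/r − 1.96)

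Example, m = 8 and ICC 0.05: DE = 1.35, r = sqrt(2.35/2) = 1.084, type I error 7.1%, power 85%.

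| ICC | r (m = 8 to 15) | Type I error | Power |
|---|---|---|---|
| 0.01 | 1.017-1.034 | 5.4-5.8% | 89-88% |
| 0.02 | 1.034-1.068 | 5.8-6.6% | 88-86% |
| 0.05 | 1.084-1.162 | 7.1-9.2% | 85-80% |
| 0.10 | 1.162-1.304 | 9.2-13.3% | 80-70% |

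At ICC 0.05 the true SE is 8-16% larger than the ANOVA's. Put the other way, the ANOVA's SE is 1 − 1/1.084 = 7.7% to 1 − 1/1.162 = 13.9% too small.

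**Step 3: other group sizes.** With groups of 6 the effect is smaller: 5.3% and 89% at ICC 0.01, 6.5% and 86% at ICC 0.05. If all 25 analysed PDH patients sat in one group, ICC 0.05 would give 12.1% and 73%. Simulating a naive two-sample test at ICC 0.05 gave 6.4% (groups of 6), 7.3% (groups of 8) and 12.0% (one group of 25), in line with the formula. The formulas are normal approximations and ignore degrees of freedom lost through having few groups, so the power figures are on the optimistic side.

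**Step 4: which remedy works with so few groups.** Simulation with 24 per arm, effect 0.917 SD and ICC 0.05:

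- A group-level test with Satterthwaite degrees of freedom had power of about 56%, 67% and 74% with two, three and four PDH groups. Its type I error was still about 8% with two groups.
- The planned comparison with its SE multiplied by r held about 5% type I error, with roughly 79-84% power, when the ICC used was the true one.

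**The case against.** Four objections have weight.

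1. **This is a condensed article.** One sentence on ANOVA does not exclude a group term in a full protocol or analysis plan that is not shown. That stands for the model details. It does not reach the printed sample size, whose formula assumes independence, or the 90% power that comes from it.
2. **The sample size is provisional.** The article says it will be revised after preliminary results, and it calls the PDH-TAR comparison a secondary goal. That stands, and it offers a natural occasion for the correction.
3. **The ICC may be small.** One group session a month against at least two family or individual sessions is about 6 against 12 or more over six months. That argues for a modest correlation. At ICC 0.01 with groups of 6 the effect is negligible.
4. **Controls may not be free of grouping.** If TAR health education is given as group lectures, some clustering would be two-armed. The therapy groups would still be described in one arm only.

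A reader might infer that the error bars are too narrow as a matter of fact and that 90% power will not be reached. The article does not support that flat reading: it gives no ICC, group size or number of groups, and with no within-group correlation the planned figures stand. A reader might also infer that a partially nested mixed model should become the primary analysis. With two to four groups, the simulation above speaks against it.

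**Conclusion.** The point holds in conditional form. Group therapy is part of PDH, none is described for TAR, and both the stated sample size and the stated test assume independent patients. For any positive within-group correlation the direction is certain: the SE is too small and the power is overstated.

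The magnitude is not fixed by the article. Over the assumed ranges it runs from trivial (ICC 0.01) to a type I error of 13.3% and power of 70% (ICC 0.10, groups of 15). The lower part of the range is the more plausible, given the balance of group and individual sessions. The figures rest on 25 analysed per arm, delta/SD back-solved as 0.917, equal group sizes and a normal approximation. This is worth correcting because it is cheap, and because membership that was never recorded cannot be used later.

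**What to change.** - **Groups.** Run the PDH group sessions in more than one group, and state how many and of what size. With a single group, the group effect is fully confounded with treatment and no model can separate them.
- **Data.** Record each PDH patient's therapy group.
- **Analysis.** Keep the planned comparison. Alongside it, report the GDS effect with the SE multiplied by sqrt((1 + DE)/2), DE = 1 + (m − 1) × ICC, at fixed ICCs of 0.01, 0.02, 0.05 and 0.10 and the actual group size. Use a partially nested mixed model (random group effect in the PDH arm only) as a supporting analysis, because with two to four groups it has low power and unstable error control.
- **Power statement.** Say that 90% power assumes no clustering. Under the assumed groups of 8 to 15 it falls to about 89-80% for ICC 0.01 to 0.05, and to 80-70% at ICC 0.10. Make this part of the sample-size revision that the article already foresees.

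The cost is a group code, one extra calculation, a somewhat wider interval in the sensitivity results and a less favourable stated power.

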**Figure 1 f1:**
[figure not shown]
The research flowchart.

## Data Collection

### Screening, Demographics, Depressive Symptoms, Quality of Life, Social Functioning, Family Functioning, and Cognitive Functioning Data

At screening, the trained investigators will examine, gather, and record participant eligibility. The Chinese version of MINI (27) will be used to confirm DSM-IV TR criteria for MDD (28) and assess substance/alcohol abuse disorders and other potential exclusion criteria. After enrollment, to investigate the risk factors of LLD, data will be collected regarding the demographics, lifestyle, medical history, sleep quality, family history of psychiatric disease, LLD course, treatment and intervention process, concurrent treatment and intervention measures, social support, negative life events, activities of daily living, interests and hobbies, local mental health resources, and KAP for LLD, using a set of questionnaires that we will design. Other data, including coping style, personality traits, and the severity of depressive symptoms, will be assessed and acquired using standardized Chinese scales and questionnaires, respectively (29, 30).

Finally, to evaluate the effectiveness of supportive PDH intervention, follow-up data regarding improvements in depressive symptoms, QOL, and social, family, and cognitive functioning will be assessed and acquired using other standardized Chinese scales and questionnaires, respectively (29–31).

### Sample Size, Power, and Effect Size

The primary goals of this study are to analyze the epidemiological characteristics and construct a risk model for LLD in Liaoning. The study design for this part is a cross-sectional study. Wang et al. reported the prevalence of MDD in elderly Chinese at 2.8%, where the ratio of urban to rural was 1.4:1 (10). That is, if the testing level α and the relative error ϵ are set to 0.05 and 0.15P, 6179 community-residing elderly adults are expected to enroll, according to the following equation (32):

$$\text{N}=[Z_{a/2}^{2}P(1-P)]/\epsilon^{2}$$

Given that 10% of the data are missing, a total of 6,800 elderly residents (approximately 3414 urban residents and 3,386 rural residents) should be included.

The secondary goals of this study are to conduct and evaluate integrated supportive PDH interventions and TAR for the objects in the trial group and control group, respectively. The study design for this part is an experimental study, and the sample size can be determined by the change in the value of the mean and standard deviation of the depression score of elderly patients before and after intervention in a previous study (33). That is, if the testing level α and type-II error β are set as 0.05 and 0.10, respectively, the sample size of the trial group and control group will be roughly 25 in both cases, according to the following equation (32):

$${\text{N}}_{1}={\text{N}}_{2}=2[\frac{({\text{z}}_{\alpha /2}+{\text{z}}_{\beta })\sigma }{\sigma }{]}^{2}$$

Given that 20% of the data are missing, each group should have a sample size of 30 LLD patients. Meanwhile, to facilitate the compliance of patients in the later intervention stages, and to ensure the effectiveness of the intervention, each patient’s primary caregiver will be required to accompany the participant. In the later stages, we will further revise the sample size according to the preliminary experimental results from the intervention study.

The participants, method, assessment time, and data collection administrators are listed in **Table 3**.

**Table 3 T3:** Data collection at baseline and follow-up evaluation.

Domain	Measure	Participants	Method	Assessment time	Administrator
Informed consent	Informed consent	All participants ^b^	Interview	Screening	Investigator
Eligibility	Inclusion/Exclusion	All participants ^b^	Interview	Screening	Investigator
Psychiatric diagnoses	MINI	All participants ^b^	Interview	Screening	Investigator
MDS for the elderly ^a^	Team-designed questionnaire	All participants ^b^	Interview	Baseline	Investigator
Coping style, personality traits	SCSQ, EPQ	All participants ^b^	Interview	Baseline	Investigator
KAP for LLD	Team-designed questionnaire	All participants ^b^	Interview	Baseline and every follow-up	Investigator
Local mental health resources and resources available to LLD patients	Team-designed questionnaire	All participants ^b^ and staff of CHS institutions	Interview	Baseline	Investigator
Treatment and intervention process, concurrent treatment and intervention measures	Team-designed questionnaire	All participants ^b^	Interview	Baseline and every follow-up	Investigator
Depressive symptoms	GDS	60 LLD patients and their primary caregivers ^c^	Interview	Baseline and every follow-up	Investigator
Quality of life	SF-36, OPQOL	60 LLD patients and their primary caregivers ^c^	Interview	Baseline and every follow-up	Investigator
Social functioning	SDSS	60 LLD patients and their primary caregivers ^c^	Interview	Baseline and every follow-up	Investigator
Family functioning	Family APGAR Scale	60 LLD patients and their primary caregivers ^c^	Interview	Baseline and every follow-up	Investigator
Cognitive functioning	MoCA, GSES, IBS	60 LLD patients and their primary caregivers ^c^	Interview	Baseline and every follow-up	Investigator

LLD, Late Life Depression; MINI, Mini-International Neuropsychiatric Interview; MDS, Minimum Data Set; SCSQ, Simplified Coping Style Questionnaire; EPQ, Eysenck Personality Questionnaire; KAP, Knowledge-Attitude-Practice; GDS, Geriatric Depression Scale; SF-36, The MOS item Short From Health Survey; OPQOL, Chinese Revised Version of Old People Quality Of Life Questionnaire; SDSS, Social Disability Screening Schedule; APGAR, Adaptability, Partnership, Growth, Affection, and Resolve; GSES, General Self-Efficacy Scale; IBS, Irritational Beliefs Scale; MoCA, Montreal Cognitive Assessment; CHS, Community health service.

a Content of MDS includes demographics, lifestyle, medical history, sleep quality, family history of psychiatric disease and LLD course, social support, negative life events, daily activities, interests, and hobbies.

b “All participants” refers to the 6,800 community-residing elderly adults.

c 30 LLD patients and their primary caregivers in the trial group, and 30 LLD patients and caregivers in the control group.

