### Enrollment, Supportive PDH Intervention, and Follow-Up

The 6800 community-residing elderly adults will be screened and enrolled by the investigators according to the inclusion and exclusion criteria. To ensure the balance and representativeness of sample sources, we intend to adopt a multi-stage sampling method. At the first stage, four cites will be randomly selected in Liaoning province by randomized sortition. At the second stage, one district and one township will be randomly selected from each selected city. At the third stage, one urban community and one village community will be randomly selected from each selected district/township. At the fourth stage, elderly residents will be selected from each selected urban community and village community with a convenient sampling method.The 60 community-residing elderly adults with LLD and their principle caregivers will be allocated to trial and control groups. In addition, we will ensure that there are no statistical differences between the two groups in term of the degree of depression, drug treatment programs, knowledge of mental health, geographic distribution, and other aspects before carrying out the interventions. The trial group of 30 elderly patients and their principle caregivers will receive the same content and frequency of individualized and group intervention for 6 months. By contrast, the 30 elderly patients in the control group and their principle caregivers will receive TAR, which are suitable for all MDD patients as routine. During this period, except for any additional treatment for comorbid physical diseases or short-lasting benzodiazepines for severe insomnia, other antipsychotic medications, systematic psychotherapy, and long-lasting benzodiazepines will not be allowed. The detailed content, forms, and methods of the supportive PDH intervention are listed in **Table 2**.

**Table 2 T2:** Content, form and method of supportive PDH interventions.

	Supportive PDH interventions

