## Discussion

Based on an analysis of the current clinical report results, there are many basic studies and investigations of the pathogenic factors of LLD. Investigations mainly focus on three groups of variables. First, researchers study the correlation between the characteristics (34, 35) (biological factors such as disease course, classification, demographics, etc.) of the disorders and their occurrence and development. Second, there is a focus on psychological factors (36, 37) (personality traits, attribution and coping style, self-esteem, etc.) and how they act on the occurrence and development of the disease. Third, researchers consider the relationship between social factors (38–40) (stressful life events, family environment, social support, marital status, economic income level, etc.) and the occurrence and development of the disease. To some extent, these studies have revealed the relationship between LLD and various influential factors, and they have identified the related variables that can predict the condition and outcome of LLD. However, few studies provide a new perspective for studying the process of integrating multiple influential research variables, while analyzing the path of interaction between variables and exploring the influence of various factors on the overall research. In our study, therefore, biological, psychological, and social factors will be integrated to analyze and predict LLD risk factors. In addition, the results will be incorporated into the system of occurrence and development of the disorder. Then, SEM of the risk factors for LLD will be constructed. Furthermore, in view of differences in the prevalence of LLD between rural and urban areas, participants will be recruited from both rural and urban sites for a broadly inclusive and representative elderly population that ensures the equilibrium of sample sources. In doing so, the results and conclusions of the study will be widely generalizable.

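### The survey fixes a near-equal urban–rural sample but names only plain percentages, so the crude Liaoning prevalence depends on the allocation

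*Protocol article*

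**What the plan says.** All references are to the protocol article.

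- *Sample Size, Power, and Effect Size* takes its inputs from a cited meta-analysis that "reported the prevalence of MDD in elderly Chinese at 2.8%, where the ratio of urban to rural was 1.4:1". With "the testing level α and the relative error ϵ are set to 0.05 and 0.15P, 6179 community-residing elderly adults are expected to enroll" and an allowance of 10% for missing data, it concludes that "a total of 6,800 elderly residents (approximately 3414 urban residents and 3,386 rural residents) should be included". It does not say what the 1.4:1 is a ratio of, or how the split was reached.
- *Objectives* names Liaoning province as the population whose epidemiology is to be described.
- *Enrollment, Supportive PDH Intervention, and Follow-Up* states that "one district and one township will be randomly selected from each selected city". No size criterion is given, and residents within each community are then taken by convenience.
- *Discussion* explains that both kinds of site are used "in view of differences in the prevalence of LLD between rural and urban areas".
- *Data Preprocessing and Statistical Analysis* presents its list as the details of the analytic approach. For description, the variables "will be described by frequency distribution, percentage, arithmetic mean, and standard deviation". It names no prevalence estimator, no stratum-specific estimate and no weighting.

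**The concern.** A pooled percentage from a stratified sample is an average of the stratum percentages, weighted by the sample shares. Where the strata differ in prevalence, it estimates the population figure only if the sample shares are close to the population shares. Here the sample shares are fixed at about 50:50 for reasons unconnected with the population, the authors expect prevalence to differ, and the result is meant to describe a province. The article calls the epidemiological description, with the risk model, its primary goal, and the 6,800 is sized for a relative error of 15% on exactly this prevalence. An error caused by the allocation does not shrink as the sample grows, and an ordinary confidence interval does not show it.

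**Working it through.** **Inputs from the article.** Urban 3,414, rural 3,386, total 6,800; overall prevalence P = 2.8%; urban-to-rural ratio 1.4:1; margin 0.15P.

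**Assumptions, not in the article.** The 1.4:1 is a ratio of prevalences and holds in Liaoning. The urban share W of Liaoning residents aged 60 and over lies between 30% and 70%.

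**1. The plan's own figures.** 3,414 + 3,386 = 6,800, so the split adds up. 3,414/3,386 = 1.008, and the urban sample share is f = 3,414/6,800 = 0.502. For the total, 6,179 × 1.10 = 6,797, or about 6,800. (The 6,179 itself is not exactly reproduced: the stated formula gives 5,927 with z = 1.96 and 6,171 with z = 2. That is a separate matter and does not affect what follows.)

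**2. Can the split be derived?** With prevalences in the ratio 1.4:1:

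- Variance-optimal allocation between strata of equal population size gives about 3,678:3,122.
- Equal relative precision gives about 2,820:3,980.
- One non-standard rule matches to rounding. With urban 2.8% and rural 2.8/1.4 = 2.0%, dividing 6,800 in the ratio (1 − 0.020):(1 − 0.028) gives 3,413.9:3,386.1. This may be the source or a coincidence; the article does not say.

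None of these rules uses the urban and rural shares of Liaoning's older population, which the article does not give.

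**3. Effect on the crude prevalence.** Let rural prevalence be p and urban prevalence 1.4p.

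- Crude expectation: p(1 + 0.4f) = p(1 + 0.4 × 0.502) = 1.2008p
- Provincial value: p(1 + 0.4W)
- Relative bias: 1.2008/(1 + 0.4W) − 1, which does not depend on p

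For percentage points, set p so that the simple average of the two strata is 2.8%: rural 2.8 × 2/2.4 = 2.33%, urban 2.8 × 2.8/2.4 = 3.27%, crude 2.80%.

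| Assumed urban share W | Provincial value | Crude minus provincial | Relative bias |
|---|---|---|---|
| 30% | 2.61% | +0.19 points | 1.2008/1.12 − 1 = +7.2% |
| 40% | 2.71% | +0.10 points | 1.2008/1.16 − 1 = +3.5% |
| 50% | 2.80% | about 0 | 1.2008/1.20 − 1 = +0.1% |
| 60% | 2.89% | −0.09 points | 1.2008/1.24 − 1 = −3.2% |
| 70% | 2.99% | −0.18 points | 1.2008/1.28 − 1 = −6.2% |

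**4. Against the planned margin.** 0.15 × 2.8% = 0.42 points. The largest relative bias in the range, 7.2%, is 7.2/15 = 48% of the relative margin.

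**The case against.** A near-equal allocation is a legitimate design. The enrolment section asks for balance and the Discussion for an equilibrium of sample sources, and equal strata serve an urban–rural comparison well. This stands: the allocation need not change, only the way the strata are combined.

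The article nowhere says that prevalence will be a crude percentage, and a condensed article often leaves weighting to a fuller document. This stands in part. It would be wrong to say that the plan commits to an unweighted estimate. But the article fixes the allocation, takes the province as target, expects the strata to differ, and lists plain percentages under what it calls the details of its analysis. Someone following that text would report a figure that depends on the allocation.

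The size rests on an urban share and a prevalence ratio that the documents do not supply for Liaoning, and it vanishes near a 50% share. This stands, and is why the result is given as a range.

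Finally, post-stratification cannot repair convenience sampling within communities, since selection probabilities are unknown, nor the Table 1 criterion that excludes people in a current depressive episode from the survey. Also true, but these are further problems and not reasons to leave this one.

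**Conclusion.** The point holds as one about estimation. Under the stated assumptions, the crude pooled prevalence would differ from the provincial value by about +7% to −6% for urban shares of 30% to 70%. That is at most about 0.19 points, against a planned margin of 0.42. The effect is modest but systematic, and it falls on a primary goal.

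A reader might go further and infer that the sample should have been split 1.4:1, that is 6,800 × 1.4/2.4 = 3,967 urban and 2,833 rural, so that 3,967 − 3,414 = 553 people are in the wrong stratum. The documents do not support this. The sentence attaches the ratio to prevalence, the Discussion also speaks of prevalence differences, and nothing says that the split follows from the ratio. Even as a head-count ratio it would describe the cited source and not Liaoning. Nor is it established that the ratio went unused, since one undocumented calculation from 2.8% and 1.4 returns the split. What can be said is that the article leaves the meaning of the ratio and the origin of the split unexplained.

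**What to change.** 1. In *Data Preprocessing and Statistical Analysis*, estimate prevalence separately for urban and rural residents. Combine the two by post-stratification to the urban–rural (and age–sex) distribution of Liaoning residents aged 60 and over, name the source of that distribution, and report the crude figure as secondary.
2. In *Sample Size, Power, and Effect Size*, say what 1.4:1 measures and how 3,414:3,386 was obtained, or state that the near-equal split is deliberate.
3. State that the weighting does not cure the convenience sampling at the last stage.

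The cost is a few sentences, a routine adjustment and somewhat larger variance. For the urban–rural weights alone, and taking the two stratum variances as equal, the variance factor is W²/f + (1 − W)²/(1 − f). At W = 30% this is 0.09/0.502 + 0.49/0.498 = 1.16, and at W = 70% it is 0.49/0.502 + 0.09/0.498 = 1.16. The standard error is then about 8% larger at the ends of the range (√1.16 = 1.08), and practically unchanged near 50%. No change to recruitment is needed.
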